## Abstract

**Background:**

Malunion is the most common complication of distal radius fracture. It has previously been demonstrated that there is a correlation between the quality of anatomical correction and overall wrist function. However, surgical correction can be difficult because of the often complex anatomy associated with this condition. Computer assisted surgical planning, combined with patient-specific surgical guides, has the potential to improve pre-operative understanding of patient anatomy as well as intra-operative accuracy. For patients with malunion of the distal radius fracture, this technology could significantly improve clinical outcomes that largely depend on the quality of restoration of normal anatomy. Therefore, the objective of this study is to compare patient outcomes after corrective osteotomy for distal radius malunion with and without preoperative computer-assisted planning and peri-operative patient-specific surgical guides.

**Methods/Design:**

This study is a multi-center randomized controlled trial of conventional planning versus computer-assisted planning for surgical correction of distal radius malunion. Adult patients with extra-articular malunion of the distal radius will be invited to enroll in our study. After providing informed consent, subjects will be randomized to two groups: one group will receive corrective surgery with conventional preoperative planning, while the other will receive corrective surgery with computer-assisted pre-operative planning and peri-operative patient specific surgical guides. In the computer-assisted planning group, a CT scan of the affected forearm as well as the normal, contralateral forearm will be obtained. The images will be used to construct a 3D anatomical model of the defect and patient-specific surgical guides will be manufactured. Outcome will be measured by DASH and PRWE scores, grip strength, radiographic measurements, and patient satisfaction at 3, 6, and 12 months postoperatively.

**Discussion:**

Computer-assisted surgical planning, combined with patient-specific surgical guides, is a powerful new technology that has the potential to improve the accuracy and consistency of orthopaedic surgery. To date, the role of this technology in upper extremity surgery has not been adequately investigated, and it is unclear whether its use provides any significant clinical benefit over traditional preoperative imaging protocols. Our study will represent the first randomized controlled trial investigating the use of computer assisted surgery in corrective osteotomy for distal radius malunions.

**Trial registration:**

NCT01193010

## Background

Despite advances in internal fixation devices, malunion of distal radius fractures is still the most common complication after wrist fractures, with overall malunion rates as high as 17% [1]. Patients with malunion of the distal radius can experience significant disability in the form of pain, arthritis, decreased range-of-motion, weakness, and visible deformity [2-7]. For those who undergo operative treatment, clinical studies have demonstrated a positive correlation between a more accurate anatomic correction and eventual overall wrist function [8-11]. However, surgical correction presents a challenge to orthopedic surgeons because of the complex anatomic deformity often associated with this condition; accurate preoperative planning is crucial for surgical success. Standard radiographs are often sufficient for simple deformities in the coronal or sagittal planes; however, the majority of distal radius fracture malunions have more than one plane of deformity [12-14]. Reformatted 3D CT reconstructed models have improved the surgeon's ability to conceptualize the multiple planes of deformity in more complex malunions; however, these models still only serve as visual templates for intra-operative referencing.

New virtual surgical planning technology that combines CT imaging and state-of-the-art software has recently been developed. To date only small case series and a case report using this technology for corrective osteotomy of malunited distal radius fractures have been published [13,15-18]. Although these studies report promising results, existing methodologies have not fully utilized available technological capabilities and there has been no study to date that compares patient outcomes using these computer assisted preoperative planning techniques to conventional pre-operative planning techniques for surgical correction of malunited distal radius fractures.

In order to understand the role that virtual surgery techniques should play in corrective osteotomy of malunited distal radius fractures, it is critical to understand how using this technology compares to conventional pre-operative planning in terms of functional outcomes, patient satisfaction, and pain.

The objectives of this study are to compare patient outcomes after corrective osteotomy for malunited distal radius fractures with and without preoperative computer-assisted planning and patient-specific surgical guides.

## Methods/Design

### Participants

All patients older than 18 years of age undergoing elective surgery for symptomatic malunited extra-articular distal radius fractures by the surgeons participating in this study will be invited to participate. Subjects will be invited to enroll during their routine preoperative office visit for care of their wrist. The protocol will be explained in detail and informed consent obtained prior to the initiation of any treatment. Patients will be given a copy of the consent form, and be informed that their participation is voluntary and that they can withdraw at any time. After discussing the risks/benefits and alternatives to participation, the patient will sign the consent form.

#### Inclusion criteria

• Adult patient (age 18 years or greater)

• Extra-articular malunion of the distal radius, following the criteria for malunion as defined by McQueen et al. [19] as one of the following compared with the opposite normal side:

○ dorsal tilt >10°

○ volar tilt >15°

○ radial shortening >3 mm

• Indications for osteotomy are pain, weakness, decreased palmar flexion, incongruency of the DRUJ and adaptive carpal instability

• At least 3 months post-injury

• Fluent in English

#### Exclusion criteria

• Intra-articular malunion with a step-off or gap >1 mm

• Associated injuries of the ipsilateral forearm

• Functional disability for any other reason than the malunion

• Pathology of the contralateral forearm

• Patients with impaired decision-making capacity

• Pregnancy

• Prisoners

### Intervention

This study is designed as a randomized controlled trial, comparing two groups of patients with symptomatic extra-articular malunited distal radius fractures (Figure 1). One group of patients will undergo corrective surgery of the distal radius, with preoperative computer-assisted planning and virtual osteotomy, and the other group will undergo corrective surgery, with conventional (non-computer-assisted) preoperative planning. In both groups, the surgeons will be restricted to using a volar plate as the fixation device for the osteotomy. Also, in both groups, if inadequate cortical apposition is obtained intra-operatively, bone graft will be used.

**Figure 1 F1:**
[figure not shown]
**Flux scheme for study**.

#### Computer-assisted planning

##### CT imaging and 3D Forearm Model Reconstruction

The first step will be to obtain CT images of both the malunited and the contralateral normal forearm. The forearms will be scanned using high-resolution axial plane images with the forearms in neutral position. The CT images will be acquired using standard clinical scanners available at each participating institution. The data obtained will consist of parallel digital images, each with a thickness of 0.625 mm, and a resolution of 512 × 512 pixels. The CT images of the forearm and wrist will be exported to a surgical planning company (SurgiCase Orthopaedics, Materialise, Leuven, Belgium) to construct a 3D anatomical model.

##### Virtual osteotomy

Surface-rendered bony models from the CT images will be created, and the virtual osteotomy will be performed. In our study, software will be used to reposition and align the osteotomy fragments to best fit the uninjured side (which will serve as a template for normal anatomy). After the osteotomy fragments have been fitted to the uninjured template, the quality inspection software will identify areas of inconsistent overlap and quantify the distance of separation between the two models. After repositioning, a virtual 3D model of the distal radius will be created.

##### Surgical guides

Two synthetic patient specific surgical guides will be manufactured (SurgiCase Orthopaedics, Materialise, Leuven, Belgium) and sterilized for use as drill and saw guides in the operating room. These drill guides are a 3D synthetic model of the radius with the position of the cut indicated will be provided to the surgeon for the procedure. The guides will be designed for use with standard locking compression plates.

##### Osteotomy Cut, Synthetic Template Spacer, and Fixation

First, the fit of the two surgical guides will be tested against the distal radius for fit. To hold the first guide in place, 1.25 m K-wires will be drilled into the small fixation holes that correspond with the temporary fixation holes on the guide. Screw holes will be drilled in the distal radius using surgical guide 1, along with metal drill guide 312.181 from Synthes. Then, surgical guide 1 will be removed, and surgical guide 2 will be fixed to the bone using K-wires, in the same fixation holes previously drilled. The osteotomy will be performed with the assistance of surgical guide 2. Next, the locking compression plate (LCP) will be fixed onto the distal bone fragment. Then, the plate will be fixed proximally onto the radial shaft. A 2.4 mm variable angle LCP two-column volar distal radius plate from Synthes, 2.4 mm/1.8 mm drill guide from Synthes, 1.25 mm K-wires, and 0.4 mm thick saw will be required for the procedure, in addition to the surgical guides provided by Materialise (Figure 2).

**Figure 2 F2:**
[figure not shown]
**Volar view of 3D reconstruction of distal radius malunion (Step 0) and the surgical procedure (Steps 1-5) that will be performed with computer-assisted planning**. Two temporary drill guides (not shown) will be used to determine the placement of the drill holes and the location of the osteotomy cut.

#### Conventional planning

Planning for the operations will be performed as usual by the surgeon, using the mirrored contralateral contour as the reconstructive goal. The planning is performed with a volar approach and the intention is to use a volar plate as a fixation device after the osteotomy. Imaging for pre-operative planning will be restricted to the standard plain radiographic views that are currently the standard of care.

After surgery, for both groups, the types of exercises and hand therapy used and the timing of their introduction will be standardized according to existing protocols that the Occupational Therapy Service has developed in conjunction with the Orthopaedic and Plastic Surgical Hand Services. One week after surgery, all study subjects will be contacted by phone by research staff to rule out any adverse post-operative events such as infection or undue pain. Outcome will be assessed at 3, 6, and 12 months after surgery during regular follow-up visits.

##### Objectives

The objective of this study is to compare patient outcomes after corrective osteotomy for malunited distal radius fractures with and without preoperative computer-assisted planning and patient-specific surgical guides. Our null hypotheses are that there is no difference between computer-assisted surgical planning and conventional surgical planning in terms of 1) functional outcome, 2) radiological outcome, and 3) economical analysis.

##### Outcomes

Functional outcome will be measured by both patient and physician-rated outcomes. Patient-rated outcomes will include the Disability of the Arm, Shoulder, and Hand (DASH) score [20], Patient Rated Wrist Evaluation (PRWE) score [21], as well as patient satisfaction and pain 10-point ordinal scales. Physician-rated outcome will be measured by bilateral range-of-motion (volar flexion, dorsal flexion, supination, pronation, radial deviation, ulnar deviation, all measured by a goniometer), bilateral grip strength (measured by grip dynamometer). Range of motion and grip strength will be performed with the elbow flexed at 90°, using a correctly calibrated JAMAR dynamometer, taking care to ensure that the subject is not leaning on the table.

Radiographic outcome will be measured on on standard PA and lateral X-rays. This will include volar angulation (°), radial inclination (°), ulnar variance (mm), and articular incongruity (mm) [22].

In both groups, the total time from surgical incision to closure will be recorded, and the total time of fluoroscopy use will be recorded.

All outcome measures will be collected preoperatively by the treating physician and/or a research assistant, and postoperatively by an independent individual.

##### Sample Size

Patient-rated functional outcome, as measured by DASH scores, is considered the most important outcome measure for patients with distal radius fractures. Our power analysis revealed that in order to detect a difference in DASH scores between the two groups with a 80% power, α = 0.05, and an estimated sigma = 10 degrees, 17 subjects will be required in each group. In order to account a lost to follow-up rate of approximately 15%, it is our goal to enroll 20 patients in each group.

##### Randomization

A random binary sequence of was generated by our research fellow (Microsoft Excel), with 0 corresponding to the control group and 1 corresponding to the experimental group. The sequence is concealed from participating surgeons. After a patient is enrolled in the study by the participating surgeon, the surgeon will email a central research coordinator, who will then assign the next number in the sequence to the study subject and inform the surgeon of the allocation. There will be no blinding. The study participants, surgeons, and other members of the research team will all be aware of the intervention group to which the participants are assigned.

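### The protocol rules out all blinding and does not exempt the independent postoperative assessor, leaving goniometer and film readings, and partly grip, open to reducible observer bias

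*Protocol article*

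**What the plan says.** The Randomization section of the protocol article closes with a categorical statement: "There will be no blinding. The study participants, surgeons, and other members of the research team will all be aware of the intervention group". It makes no exception for outcome assessment.

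The Outcomes section describes who measures: "All outcome measures will be collected preoperatively by the treating physician and/or a research assistant, and postoperatively by an independent individual". The measures covered are of two kinds:

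- **Rated by the patient:** DASH, PRWE, and the satisfaction and pain scales.
- **Read or recorded by an observer:** for the wrist, "Physician-rated outcome will be measured by bilateral range-of-motion" (by goniometer) and grip strength by dynamometer; for the X-rays, "This will include volar angulation (°), radial inclination (°), ulnar variance (mm), and articular incongruity (mm").

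The Objectives section sets null hypotheses on "1) functional outcome, 2) radiological outcome, and 3) economical analysis". The Sample Size section says "Patient-rated functional outcome, as measured by DASH scores, is considered the most important outcome measure" and bases the calculation on it.

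On the operation, the Intervention section says "In both groups, the surgeons will be restricted to using a volar plate as the fixation device for the osteotomy".

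**The concern.** Surgeons cannot be masked in this trial. That does not oblige the trial to leave the measurer unmasked, yet the open-label statement reaches past patients and surgeons to the rest of the research team. A separate postoperative assessor is already planned. Independence from the surgeon is useful, but it is not the same as not knowing the arm.

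Goniometer readings and angles drawn on radiographs call for observer judgement. The Abstract and Discussion show that better results are hoped for from computer-assisted planning, so an observer who knows the arm may shade readings in that direction. Film measurements carry particular weight: radiological outcome is a stated hypothesis, and the Background presents accuracy of anatomical correction as the link between the technique and wrist function. Biased film readings would therefore distort both a hypothesis test and the explanation of any functional result.

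**Working it through.** **Step 1. Is anyone exempt from the open-label statement?** The Randomization section says there is no blinding, then lists participants, surgeons and other research team members as aware. The Outcomes section says that outcomes are collected "postoperatively by an independent individual". It does not say whether that individual belongs to the research team or is kept from the allocation. No section provides for masked examination or masked film reading. The first statement is unqualified and the second offers no exemption, so an aware assessor is the likelier reading, though it is not stated in terms.

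**Step 2. Which outcomes would masking protect?**

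| Outcome | Who determines the value | Effect of masking the assessor |
|---|---|---|
| DASH, PRWE, pain, satisfaction | Patient, aware of arm | None |
| Grip strength | Patient effort, plus the assessor's conduct of the test | Partial |
| Range of motion | Assessor's goniometer reading, possibly patient effort (active or passive motion is not specified) | Substantial for the reading itself |
| Radiographic measures | Film reader | Largest, if the film does not reveal the arm |

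**Step 3. Could a film reveal the arm?** Both arms receive a volar plate. For the computer-assisted arm, the section on the osteotomy cut and fixation names a particular plate model and describes K-wire holes for the guides. The Intervention and Conventional planning sections require only a volar plate for the conventional arm, with no model named. Coded films may therefore still give hints if implants differ.

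**Step 4. The plan's own sample size.** Inputs from Sample Size and Statistical Methods: 80% power, two-sided α = 0.05, SD 10, 17 per group, 15% loss, 20 enrolled per group.

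- No difference to detect is stated, so 17 cannot be reproduced from the stated inputs alone. Solving the two-sample t-test backwards for n = 17 gives a difference of 9.9 points. With an assumed difference of 10 it gives 16.7, rounded up to 17.
- Allowance for loss: 17 / (1 − 0.15) = 20, which agrees.

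Masking the assessor changes none of these figures. They are used only to set n below.

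**Step 5. Illustration of what a biased reading could do.** Assume no true effect and a constant reading shift of b within-group SDs between the arms. The t statistic then has 2n − 2 degrees of freedom and noncentrality b × √(n/2). The table gives the probability of two-sided p < 0.05. For n = 17, √(17/2) = 2.915; for n = 20, √(20/2) = 3.162.

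| Assumed shift b | Noncentrality, n = 17 | P(p < 0.05), n = 17 | Noncentrality, n = 20 | P(p < 0.05), n = 20 |
|---|---|---|---|---|
| 0 | 0 | 5.0% | 0 | 5.0% |
| 0.1 | 0.292 | 5.9% | 0.316 | 6.1% |
| 0.2 | 0.583 | 8.7% | 0.632 | 9.5% |
| 0.3 | 0.875 | 13.6% | 0.949 | 15.2% |
| 0.5 | 1.458 | 29.3% | 1.581 | 33.8% |

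The rates apply to each outcome separately. They rise with n, so enrolling more patients does not remove the problem. The shifts are assumptions. The only SD in the article belongs to the DASH calculation, so the shifts cannot be converted to degrees or millimetres from the document.

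**The case against.** The other side has several fair points.

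- **The assessor's awareness is inferred.** A reader might take the protocol to say outright that the person measuring outcomes knows the arm. It does not: the independent individual is not named among those aware. This stands as a caution on wording. It does not remove the point, because the no-blinding statement is unqualified. If the assessor is in fact masked, the two sections need reconciling.
- **The operations are not identical.** A reader might infer from the shared volar plate that neither wrist nor film could reveal the arm. The documents do not support that, given the named plate and guide fixation holes in one arm and an unspecified plate in the other. Masking will be imperfect. Imperfect masking is still better than none.
- **Grip is only partly protectable.** Effort comes from an unblinded patient. This stands, and active motion would share the limit.
- **The outcome used for sizing is untouched.** DASH gains nothing from the change. This stands, and it limits the weight of the point.
- **The illustrated error rates are not evidence about this trial.** A reader might infer that the trial has a false-positive rate near 29%. Nothing in the document supports any particular shift, nor one common shift for goniometer, dynamometer and film readings.

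It might also be said that an article condenses a fuller protocol. That carries little weight here, because the absence of blinding is stated, not merely left out.

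**Conclusion.** The point holds in a limited form. As written, the plan excludes all blinding and exempts nobody, so goniometer and radiographic readings, and grip to a lesser degree, are exposed to observer bias that could be reduced. One of the three hypotheses and the observer-measured part of functional outcome are affected; the patient-rated outcomes, including DASH, would not be protected by any change to the assessor.

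The conclusion rests on reading the no-blinding statement as covering the assessor, which is likelier but not explicit. The size of the bias is unknown, and the calculated rates show only how a shift would act if there were one; they should not add to the seriousness of the point. The change is worth making and does not threaten the trial's main comparison.

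**What to change.** Three changes to the text would do it:

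1. In Randomization, limit the open-label statement to patients, surgeons and the coordinator who issues the allocation.
2. In Outcomes, state that the independent assessor is kept unaware of the allocation where feasible, and that patients are asked not to disclose it.
3. Have that assessor measure the radiographs from coded, de-identified films, in random order and without access to the chart.

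Suspected unmasking, whether from a patient's remark or from the appearance of the implant, should be logged and reported.

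The cost should be small: a masking instruction, film coding and a log. No patients, visits or additional assessor role are added, and sample size, power and α do not change. The article does not say who the independent individual is, how many there are across centres or which records they see, so each site would have to confirm that masking is workable. The remaining drawback is incomplete masking, for the reasons given above.

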##### Statistical Methods

All data will be tested for normality (Gaussian-shaped distribution) using the Komogorov-Smirnov test and homogeneity of variant by Bartlett's test. ANOVA and Tukey tests will be used for variables conforming to a normal distribution. Otherwise, nonparametric procedures (including the Kruskal-Wallis and Wilcoxon tests) will be used. For all statistical tests, differences where p < 0.05 (two-tailed) will be considered significant. The SPSS statistical package will be used for the analysis of the data (version 15.0, SPSS Inc., Chicago, IL). The power and sample size calculations have been performed with use of the nQuery Advisor software program (version 5.0, Statistical Solutions, Boston, MA).

This study will be reported according to CONSORT guidelines [23].

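### The named group tests make no use of the preoperative values the trial collects, which costs precision at about 17 evaluable patients per arm; how the three visits are handled is left open

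*Protocol article*

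**What the plan says.** All references are to the protocol article.

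- **Outcomes:** "All outcome measures will be collected preoperatively by the treating physician and/or a research assistant". Operative time and fluoroscopy time are also recorded; by their nature they have no preoperative value.
- **Conventional planning** (the paragraph on both groups after surgery): "Outcome will be assessed at 3, 6, and 12 months after surgery during regular follow-up visits".
- **Statistical Methods:** "ANOVA and Tukey tests will be used for variables conforming to a normal distribution". Variables that fail the normality check go to nonparametric procedures, with Kruskal-Wallis and Wilcoxon given as examples. For every test, "differences where p < 0.05 (two-tailed) will be considered significant". The section mentions no baseline covariate, change score, repeated-measures model or analysis visit.
- **Sample Size:** the aim is to "detect a difference in DASH scores between the two groups" with "80% power, α = 0.05, and an estimated sigma = 10 degrees", and "17 subjects will be required in each group". Twenty per group are to be enrolled to allow for about 15% loss. The size of the difference is not stated.

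**The concern.** Each patient contributes a preoperative value and up to three postoperative values, but the named tests compare groups on a single value and do not use the first measurement. In a trial of 40 patients the preoperative score is the cheapest source of precision available. It also absorbs chance differences between arms at baseline, which a plain random sequence in so small a trial can easily produce.

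The test names do not match the design closely either. Tukey's procedure adds nothing to a comparison of two arms, and with two arms Kruskal-Wallis amounts to the rank-sum test. A reader therefore cannot tell whether visit is meant to be a factor. If it were, and the repeated values were treated as independent, the group comparison would count each patient three times.

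**Working it through.** **Inputs from the article.** Two-sided α 0.05; power 80%; SD 10 (printed in degrees, taken here as DASH points); 17 evaluable per arm; three follow-up visits.

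**Assumptions, because the article gives no figure.** Difference δ = 10 DASH points, chosen because it reproduces 17 per arm; baseline/follow-up correlation ρ from 0 to 0.7; within-patient correlation between visits (ICC) from 0.3 to 0.9.

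**1. The article's own figure.** Standard error of the difference = SD·√(2/n) = 10·√(2/17) = 3.43. Noncentrality = 10/3.43 = 2.92 on 32 df, which gives power 80.7%. The exact two-sample t calculation needs 17 per arm (the normal approximation gives 16). Enrolment is 17/0.85 = 20. The stated sample size is thus what an unadjusted two-group comparison requires.

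**2. Adjusting for preoperative DASH.** Residual SD = 10·√(1 − ρ²), with df = 2n − 3 = 31.

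| ρ (assumed) | Residual SD | Noncentrality | Power at 17 per arm | n per arm for 80% | Detectable difference at 17 per arm |
|---|---|---|---|---|---|
| 0 | 10.00 | 2.92 | 80.6% | 17 | 9.9 |
| 0.3 | 9.54 | 3.06 | 84.1% | 16 | 9.5 |
| 0.5 | 8.66 | 3.37 | 90.3% | 13 | 8.6 |
| 0.7 | 7.14 | 4.08 | 97.7% | 10 | 7.1 |

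The variance falls by ρ²: 9%, 25% and 49% in the last three rows. If ρ were zero, the cost would be one degree of freedom (80.7% to 80.6%). The formula leaves out the small extra variance that comes from chance baseline imbalance, so the adjusted figures are slightly generous. They describe ANCOVA at a single visit.

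**3. Chance imbalance.** If the preoperative SD is also 10, the difference in baseline means has a standard error of 3.43. A gap above 5 points in either direction has z = 5/3.43 = 1.46, a probability of about 15%. At ρ = 0.5 such a gap moves the unadjusted estimate by 0.5 × 5 = 2.5 points. This is part of the ordinary sampling error of the unadjusted test, not a bias in it.

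**4. Handling of visits.** Simulation under no effect, 17 per arm, three visits, equal correlation between visits, 50,000 runs per ICC value. The design effect is 1 + 2·ICC.

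| ICC (assumed) | Design effect | Type I error if visits are independent rows | Each visit tested separately | At least one of three visits significant |
|---|---|---|---|---|
| 0.3 | 1.6 | 12% | 5% | 14% |
| 0.5 | 2.0 | 17% | 5% | 13% |
| 0.7 | 2.4 | 21% | 5% | 11% |
| 0.9 | 2.8 | 25% | 5% | 8% |

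The third column applies only to an analysis that the article does not describe. The last column would matter only if no single visit were designated in advance.

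**The case against.** The strongest reply has four parts.

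**This is a condensed article.** Covariates and the model for repeated visits may be set out in a full protocol or analysis plan that is not shown, and naming a family of tests does not say that baseline will be ignored. This stands in part. Silence on covariance structure or partial follow-up is no fault here. But the article does commit to particular tests, and none of them, as named, uses baseline. That commitment can fairly be commented on.

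**An unadjusted comparison is legitimate.** This stands fully. Randomisation makes it unbiased, its 5% level already allows for chance imbalance, and it agrees with the sample size calculation. A reader might infer that the trial is invalid or underpowered for want of adjustment; on the article's own SD and the assumed 10-point difference, it is neither.

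**The false-positive reading goes beyond the text.** A reader might infer from ANOVA and Tukey that the three visits will be pooled and the error rate inflated. The article never says so. One ANOVA per visit holds 5% per test, and the unqualified word ANOVA does not exclude a repeated-measures version. Nor must Tukey be aimed at visits: the Abstract describes a multi-center trial and the Ethics section refers to further sites beyond the two already approved, so site is another possible factor with several levels. Wilcoxon is also unqualified and could mean the paired test. This objection stands.

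**The gain depends on an unknown correlation.** True. At 0.3 it is about three percentage points of power; it becomes substantial from about 0.5.

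**Conclusion.** The point holds as one of efficiency and clarity, not of validity. The tests named in Statistical Methods give no role to preoperative values that the Outcomes section says are collected, and with about 17 evaluable patients per arm that wastes precision. At SD 10 and an assumed difference of 10 points, power would rise from about 81% to 84%, 90% or 98% for correlations of 0.3, 0.5 or 0.7. The gain is small at the low end and material from about 0.5.

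The handling of the three visits is unstated. Inflation of type I error to about 12% to 25% is conditional on entering visits as independent rows, and the documents do not support a claim that this is planned. The difference of 10 points and every correlation used are assumptions; only the SD, α, power and group sizes come from the article.

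**What to change.** In Statistical Methods, replace ANOVA and Tukey for the two-arm comparison with the following.

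- **DASH:** analyse it at one prespecified visit, adjusted for preoperative DASH, and report the treatment difference with a 95% CI. Either ANCOVA at that visit, or a mixed model with treatment, visit, treatment-by-visit and baseline that accounts for repeated values within a patient, would serve. Site and baseline-by-visit terms are not needed to meet this point and are debatable with about 34 completers (2 × 17).
- **PRWE, grip strength, motion and radiographic measures:** use the same baseline adjustment.
- **Ordinal pain and satisfaction scales, and operative and fluoroscopy time if non-normal:** keep a rank-based two-group test. The two times cannot be baseline-adjusted.
- **Tukey:** drop it, since it adds nothing with two arms.

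The cost is a change of wording, made before outcomes are examined because the trial is unblinded. No extra patients, visits or measurements are needed, and the 17 per arm can stand. If the full protocol or analysis plan already specifies such a model, bringing the article's sentence into line with it is enough.
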